### Sample size calculation

Sample size is based on our previous MRI study demonstrating intraneural signal reduction after neurodynamic exercises [25]. Conservatively assuming a 30% smaller effect size (within subjects repeated measures ANOVA with 3 groups & 2 time points), *n* = 63 patients are required (*n* = 21 per group, d = 0.22, power = 80%, alpha = 0.05). To account for a 20% drop out rate, we will include 78 participants (26 per group). We will include 30 healthy participants to establish normative data.

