### Assignment of interventions and blinding

Patients will be randomly assigned to one of three interventions after their first baseline appointment. Assignment will be randomised and stratified by electrodiagnostic test severity (mild/moderate) using an online tool (https://www.randomizer.org) and implemented in REDcap. The allocation ratio will be 1:1:1. The examiner performing the outcome measures will be blinded. The central research team, including the statistician, will also be blinded.

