### Statistical analysis

Data will be analysed using R Studio (v 7.2, RStudio, Boston, USA) [58]. The distribution of the data will be checked for normality, and parametric, or non-parametric methods will be used as appropriate. Participants’ characteristics in each group will be described at baseline.

Two-way repeated measures ANCOVAs (factors time and intervention, adjusted for baseline measurements as a continuous covariate) followed by post-hoc testing will be performed to identify differences in primary/secondary outcome measures among groups and over time. If there is deviation from normality, we will use non-parametric alternatives (i.e. ranked ANCOVA).

If the missing values mechanism is likely to be missing at random (MAR) or missing completely at random (MCAR), we will perform multiple imputation by chained equations. The appropriate model will be fitted in all the completed datasets, then coefficient estimates and standard errors will be pooled across imputations using Rubin’s rules.

The level of statistical significance will be set at *p* = 0.05. Adjustments for multiple comparisons will be used as appropriate.

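### The sample-size paragraph's d = 0.22 does not give 80% power for a between-arm difference with 21 per arm; effect-size scale, powered term and correlation need stating

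*Protocol article*

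**What the plan says.** The Sample size calculation section of the protocol article takes its effect from the group's earlier MRI study of neurodynamic exercises, reduced by 30%. It names the method as "within subjects repeated measures ANOVA with 3 groups & 2 time points", concludes that "63 patients are required", and gives the inputs as "21 per group, d = 0.22, power = 80%, alpha = 0.05". The total is then raised to 78 (26 per group) for dropout.

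The section does not say whether the powered term is the change over time or the group-by-time interaction. It gives no correlation between baseline and follow-up, and it does not give the earlier study's effect or its scale.

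Under Assignment of interventions and blinding, "The allocation ratio will be 1:1:1". Under Statistical analysis, the primary and secondary outcomes are to be analysed by "Two-way repeated measures ANCOVAs (factors time and intervention, adjusted for baseline measurements as a continuous covariate"), followed by post-hoc tests. The Background sets the question as exercise compared with a positive control (steroid injection) and a negative control (advice), which is a between-arm question.

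**The concern.** The letter d normally denotes a standardised mean difference. In a three-arm trial asking whether exercise differs from steroid injection and from advice, a reader will take d = 0.22 as the between-arm difference the trial can detect with 80% power. Twenty-one per arm is far too few for that.

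What is at stake is how a null result on fractional anisotropy is read. If 0.22 SD is taken as the design's sensitivity, a null result would seem to exclude quite small effects, when the trial can reliably detect only much larger ones.

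**Working it through.** **Inputs from the article:** effect 0.22, 63 patients (21 per arm, 1:1:1), 80% power, alpha 0.05, 3 groups, 2 time points.

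**Assumed, because the article does not give it:** the baseline-to-follow-up correlation rho, shown over a range. SD means the SD at a single time point unless stated.

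**Step 1. Try to reproduce 63.** For repeated measures ANOVA with m = 2 time points, the noncentrality is lambda = f² × N × m / (1 − rho). The interaction has 2 and N − 3 degrees of freedom; the time effect has 1 and N − 3. For example, f = 0.22, N = 63 and rho = 0.40 give lambda = 0.0484 × 63 × 2 / 0.60 = 10.16 and power 80.1%.

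| Reading of 0.22 | Term | rho that returns 63 | Power at N = 63 |
|---|---|---|---|
| f = 0.22 | group × time | about 0.40 | 80.1% |
| d = 0.22, so f = d/2 = 0.11 | group × time | about 0.85 | 80.1% |
| f = 0.22 | time | about 0.25 | 80.1% |
| d = 0.22, so f = 0.11 | time | about 0.81 | about 80% |

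At rho = 0.5, f = 0.22 for the interaction gives 87.2% power at 63, and 54 patients would suffice. So 63 does not follow from the printed inputs alone, even when 0.22 is taken as f.

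**Step 2. What the interaction readings imply between arms.** With two time points, f is half the SD of the three arms' mean changes, in units of the single-time-point SD.
- One arm differs from the other two by D: f = (D/2) × √(2/9) = 0.2357 D.
- Arms evenly spread, extremes D apart: f = (D/2) × √(1/6) = 0.2041 D.

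Hence f = 0.22 means D = 0.22/0.2357 = 0.93 SD to 0.22/0.2041 = 1.08 SD. And f = 0.11 means D = 0.47 to 0.54 SD.

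**Step 3. Take 0.22 as the between-arm difference.** For two arms of 21 compared by ANCOVA, the residual SD is √(1 − rho²) and the noncentrality is 0.22/√(1 − rho²) × √(21/2) (noncentral t, two-sided 0.05).

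| rho | 0.3 | 0.5 | 0.7 | 0.8 | 0.9 |
|---|---|---|---|---|---|
| Power | 11% | 13% | 16% | 21% | 36% |

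Power reaches 80% only at rho of about 0.97. The three-arm interaction agrees: with a largest difference in change of 0.22 SD, power at N = 63 is 8.8% to 10.2% at rho 0.5 and 26.6% to 34.3% at rho 0.9, again needing rho of about 0.97 for 80%.

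**Step 4. The time-effect readings.** If f = 0.22 and rho = 0.25 were used for the time effect, the same 63 patients give the interaction, at the same f, 70.2% power. If d = 0.22 and rho = 0.81 were used, a largest between-arm difference in change of 0.22 SD has only 16% to 20% power.

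**Step 5. What 21 per arm can detect.** Solving Step 3 for the difference between two arms that gives 80% power, before any multiplicity adjustment: 0.81 SD at rho 0.4, 0.77 SD at rho 0.5 and 0.63 SD at rho 0.7.

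**The case against.** The strongest reply is that the sentence names its test. It describes a repeated measures ANOVA with a within-subject element, not a two-sample comparison, so the low power in Step 3 belongs to a calculation the authors did not claim to have made. On this view the fault is at most a wrong letter on an effect size, and the missing correlation is a detail an article may leave to the full protocol. Much of this stands. The absent correlation is not a fault in itself, and the wording does fit a pooled time effect. But the article prints effect size, sample size, power and alpha together, and under the printed symbol they do not agree for the comparison the trial exists to make. No reading in Step 1 gives 80% power for a 0.22 SD difference between arms.

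Several stronger inferences are tempting and are not supported:

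- **That 0.22 can only be an ANOVA f.** Step 1 shows two routes to 63 with d = 0.22 converted to f = 0.11. So the 0.93–1.08 SD figure belongs to one reading only and is not the trial's established sensitivity.
- **That rho = 0.40 was the assumption used.** That value is worked backwards from 63; nothing in the article supports it over 0.25, 0.81 or 0.85.
- **That "Conservatively assuming a 30% smaller effect size" is misleading.** The adverb describes a cut from the earlier study's effect, which is cautious relative to that estimate on any scale.
- **That 78 fails to cover the dropout.** 78 × 0.8 = 62.4 against 63 is rounding.
- **That the authors would over-read a null result.** The article says no such thing; the risk lies in how readers would use the printed figure.

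**Conclusion.** The point holds in a limited form. As a between-arm standardised difference, d = 0.22 is incompatible with 21 per arm and 80% power unless baseline and follow-up correlate at about 0.97; across correlations of 0.3 to 0.9 the power is 11% to 36%. Either the effect size is mislabelled, or it is on another scale, or the calculation powers a change over time that does not answer the three-arm question. The article does not allow a choice among these.

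On the planned baseline-adjusted analysis, 21 per arm detects about 0.81 SD at correlation 0.4 and 0.77 SD at 0.5, roughly 3.5 to 3.7 times 0.22 (0.77/0.22 and 0.81/0.22). These figures assume equal arms of 21, a common SD and an unadjusted two-sided 0.05 comparison of two arms; a multiplicity adjustment would raise them, and a higher correlation would lower them. The finding does not show that the trial needs more patients. It shows that its stated sensitivity cannot be relied on as printed.

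**What to change.** Restate the sample size paragraph so that it:

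1. labels 0.22 correctly as d or f, with the SD to which it refers;
2. names the group-by-time (between-arm) effect as the powered term;
3. gives the correlation actually used in the calculation, not one chosen afterwards to return 63;
4. reports the between-arm difference in fractional anisotropy that 21 per arm can detect with 80% power under the planned baseline-adjusted analysis (about 0.81 SD at correlation 0.4, 0.77 SD at 0.5), so that a null result is not read as excluding 0.22 SD.

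If the calculation was in fact for the time effect, say so and restate the power for the interaction; with f = 0.22 and correlation 0.25 that is 70%.

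This is rewording only. It adds no patients and changes no procedure. The cost is a stated sensitivity that looks less favourable than the present one.

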### Statistical analysis

Data will be analysed using R Studio (v 7.2, RStudio, Boston, USA) [58]. The distribution of the data will be checked for normality, and parametric, or non-parametric methods will be used as appropriate. Participants’ characteristics in each group will be described at baseline.

Two-way repeated measures ANCOVAs (factors time and intervention, adjusted for baseline measurements as a continuous covariate) followed by post-hoc testing will be performed to identify differences in primary/secondary outcome measures among groups and over time. If there is deviation from normality, we will use non-parametric alternatives (i.e. ranked ANCOVA).

If the missing values mechanism is likely to be missing at random (MAR) or missing completely at random (MCAR), we will perform multiple imputation by chained equations. The appropriate model will be fitted in all the completed datasets, then coefficient estimates and standard errors will be pooled across imputations using Rubin’s rules.

The level of statistical significance will be set at *p* = 0.05. Adjustments for multiple comparisons will be used as appropriate.

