**Methods:**

This mechanistic, randomised, single-blind, controlled trial will include 78 people with electrodiagnostically confirmed mild or moderate CTS and 30 healthy participants (*N* = 108). Patients will be randomly assigned into (1) a 6-week progressive home-based neurodynamic exercise intervention (*n* = 26), (2) a steroid injection (= 26), or (3) advice (*n* = 26) group. The primary outcome measure is fractional anisotropy of the median nerve at the wrist using advanced magnetic resonance neuroimaging. Secondary outcome measures include neuroimaging markers at the wrist, quantitative sensory testing, electrodiagnostics, and patient reported outcome measures. Exploratory outcomes include neuroimaging markers at the cervical spine, inflammatory and axonal integrity markers in serial blood samples and biopsies of median nerve innervated skin. We will evaluate outcome measures at baseline and at the end of the 6-week intervention period. We will repeat questionnaires at 6-months. Two-way repeated measures ANCOVAs, followed by posthoc testing will be performed to identify differences in outcome measures among groups and over time.

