### Study procedure

Consented participants (see ethics below) will receive the baseline set of questionnaires to complete before the first baseline appointment at the Nuffield Department of Clinical Neurosciences, University of Oxford. This first appointment will include a detailed bedside neurological assessment and measures of nerve function. If participants present with bilateral symptoms of CTS, the most affected hand will be evaluated. At this point, participants not meeting the inclusion criteria will be excluded from the study (e.g., severe electrodiagnostic test findings). Eligible participants will provide a blood sample and a finger skin biopsy.

Participants will be invited for a second baseline appointment for an MRI of the wrist and the neck. Following the scan, patients will receive their assigned intervention. After the 6-week intervention period, patients will be invited for a follow-up appointment to repeat the same assessments. Finally, questionnaires will be sent out to patients at 6 months (Fig. 1).

Healthy controls will only attend the baseline appointments during which the same measures will be performed as in patients.

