### Primary mechanistic outcome measure

#### Magnetic resonance neurography (MRN): Fractional Anisotropy (FA)

All participants will attend a MRN session on a 3 Tesla MAGNETOM Prisma scanner (Siemens, Germany) to visualise the median nerve at the wrist using a dedicated 16-channel wrist coil (Siemens, Germany).

Participants will be positioned in a ‘superman’ position, lying prone with the wrist above their head resting in the centre of the bore. The protocol includes the acquisition of multishell (b = 0, b = 300 and 800 s/mm^2^) diffusion-weighted imaging scans. In addition, true fast imaging with steady-state free precession (TRUFI) with/without magnetisation transfer (MT) preparation, and T2-mapping scanning will be acquired (see other markers in MRN). Scan parameters are summarised in Table 1.

**Table 1 Tab1:** MRI sequence parameters at the wrist

	3D TRUFI	T2 mapping	Diffusion Weighted Imaging (DWI)
Repetition time (TR)	10.1 ms	7,110 ms	4,000 ms
Echo time (TE)	4.14 ms	14.7–147 ms	47 ms
Flip angle (FA)	20°	Variable	90° and 180°
Field of view (FoV)	74.3 mm	225 mm	160 mm
Dimensionality	3D	2D	2D
Slice thickness	0.6 mm	1 mm	1 mm
Number of slices	176	50	50
In-plane resolution	0.1 × 0.1 mm	0.5 × 0.5 mm	1 × 1 mm
Echo spacing	N/A	N/A	0.96ms
Fat suppression	No fat saturation	Fat saturation	Fat saturation
Parallel acquisition technique	GRAPPA factor 2	GRAPPA factor 2	GRAPPA factor 2
Bandwidth	350 Hz/Px	132 Hz/Px	1220 Hz/Px
b values	N/A	N/A	0 (NSA = 8), 300 (NSA = 5), 800 (NSA = 8)
No. signal averages	1	1	8 (b = 0), 5 (b = 300), 8(b = 800)
Scan time single phase-encode blip (right-left or left-right)	N/A	N/A	6.42, 7.42
Total scan time (min)	10.16	10.32	14.18

N/A: not applicable; NSA: number of signal averages

All diffusion image pre-processing will be performed using the FMRIB Software Library (FSL) Diffusion Toolbox v 6.0 (Oxford, UK). Briefly, TOPUP [42, 43] and EDDY [44] tools will be applied to correct for distortions and eddy currents followed by DTIFIT [45] to compute the diffusion tensor model. FLIRT will be used to co-register the diffusion metrics to the anatomical sequences.

Median nerve region of interests will be determined at three levels: the distal radio-ulnar joint (proximal), pisiform (mid-carpal tunnel) and hook of hamate (distal carpal tunnel). Fractional anisotropy (no units) will be computed as our primary outcome measure.

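### For FA, the repeated measures ANCOVA makes baseline both a response and its own covariate, so the error rate and power of the primary test rest on an unstated choice of fit and tested term

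*Protocol article*

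**What the plan says.** The Statistical analysis section fixes one model for all primary and secondary outcomes: "Two-way repeated measures ANCOVAs (factors time and intervention, adjusted for baseline measurements as a continuous covariate"), followed by post-hoc tests. Its stated aim is "to identify differences in primary/secondary outcome measures among groups and over time". No single term (group, time or their interaction) is named as the primary test, and nothing is said about a covariate-by-time term.

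The primary outcome is set in the section on magnetic resonance neurography: "Fractional anisotropy (no units) will be computed as our primary outcome measure". On timing, the abstract says: "We will evaluate outcome measures at baseline and at the end of the 6-week intervention period". The only later contact is described under Study procedure: "Finally, questionnaires will be sent out to patients at 6 months". FA therefore has two measurements, one of them baseline. The Sample size calculation matches this, being based on a "within subjects repeated measures ANOVA with 3 groups & 2 time points" with no covariate mentioned.

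**The concern.** A time factor needs at least two levels. For FA, and for the other outcomes measured only at baseline and 6 weeks, the second level can only be baseline. The baseline value then sits on both sides of the model. In the baseline rows the outcome equals the covariate, so the slope is 1 and there is no error. In the 6-week rows the slope is the baseline to 6-week correlation, rho (equal variances assumed), with real error. One common slope and one residual variance cannot describe both. If time is taken to mean post-baseline visits only, FA has one visit and the factor disappears.

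At stake is the primary inference. Several fits answer to the same sentence, and they differ in false-positive rate, in power and in what the estimate means. Choosing among them after the data are seen would leave the primary test open.

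**Working it through.** **Inputs.** From the Sample size calculation: 63 patients (21 per group), effect size 0.22, power 80%, alpha 0.05, 3 groups, 2 time points. Assumptions, because the protocol does not give them: rho (varied from 0.3 to 0.7); normal data with SD 1 at both visits; and 0.22 read as Cohen's f, although it is labelled d. For f = 0.22 the root-mean-square group shift at 6 weeks is 2 × 0.22 = 0.44 SD. Effects of 0, 0.93 and 0.93 SD (advice, exercise, steroid) give this: 0.93 × √2/3 = 0.44.

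**Step 1: the plan's own figure.** For the group-by-time test, the noncentrality is f² × N × 2/(1 − rho), with 2 and 60 df. At rho = 0.4 this is 0.0484 × 63 × 2/0.6 = 10.16, and power is 0.801. For 80% power, N is 75, 63, 54 and 45 at rho = 0.3, 0.4, 0.5 and 0.6. The stated 63 is thus reproduced only if rho is about 0.40, a value that the protocol does not give.

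**Step 2: pooled or random-intercept fit, group-by-time test.** The common slope settles at (1 + rho)/2.
- The baseline residual is y0 × (1 − rho)/2, with variance ((1 − rho)/2)².
- The 6-week residual has variance (1 − rho²) + ((1 − rho)/2)².
- Their average is (1 − rho)(3 + rho)/4. The fit therefore takes the variance of a change as (1 − rho)(3 + rho)/2, while the true value is 2(1 − rho).
- The test statistic is inflated by 4/(3 + rho), so the large-sample type I error is 0.05 raised to the power (3 + rho)/4.

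A random intercept does not repair this. The two residuals have covariance −((1 − rho)/2)², which is negative, so the intercept variance is estimated at zero in 98% to 100% of simulated trials for rho from 0.3 to 0.7.

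| rho | Large-sample formula | Simulated, 21 per arm |
|---|---|---|
| 0.3 | 0.085 | 0.087 |
| 0.4 | 0.078 | 0.080 |
| 0.5 | 0.073 | 0.073 |
| 0.6 | 0.068 | 0.071 |
| 0.7 | 0.063 | 0.066 |

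**Step 3: classical error-strata fit, group-by-time test.** With two times, this test is the arm comparison of change scores. The covariate is constant within a patient and drops out. Type I error is correct (0.048 to 0.052 simulated). Power compares as follows with ANCOVA on the 6-week value, whose noncentrality is N × 0.44²/(1 − rho²) with 2 and 59 df:

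| rho | Group-by-time (change score) | ANCOVA |
|---|---|---|
| 0.3 | 0.73 | 0.90 |
| 0.4 | 0.80 | 0.92 |
| 0.5 | 0.87 | 0.95 |
| 0.6 | 0.94 | 0.975 |

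The noncentralities are in the ratio 2/(1 + rho). At rho = 0.4 this is 14.52/10.16 = 1.43.

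**Step 4: fits that do no harm to the test.**
- Adding covariate-by-time turns the interaction into a regression of y1 − y0 on arm and y0. This differs from the regression of y1 on arm and y0 only by shifting the slope by 1.
- The between-subject group main effect regresses (y0 + y1)/2 on arm and y0.

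Both give the ANCOVA F exactly (largest difference about 1e-14 in 60 simulated data sets). The main-effect estimate, however, is half the 6-week difference: 0.93/2 = 0.465.

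**The case against.** The strongest reply is that the sentence is a condensed description covering every outcome, and that ordinary fits of it are sound. A covariate-by-time term, or the between-subject group effect, yields the ANCOVA test, and the text excludes neither. That stands. A reader might infer that the model must either inflate type I error or lose power; the document does not support this.

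Two further inferences also fail. One is that group-by-time is the declared primary test: the protocol names no term. The other is that the trial is underpowered: the sample size was computed for a repeated measures ANOVA, and the change-score test delivers the planned 80% at rho near 0.40. The loss is relative to a better analysis, not to the plan. The halved main effect is likewise a matter of scaling; its F-test is valid.

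It is also fair that the sentence can describe a sound model for the questionnaires, which have both 6-week and 6-month values. They are listed among the secondary mechanistic outcomes, so the criticism does not reach every such outcome.

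What remains is that, for FA, the article states a model rather than leaving one to be specified elsewhere, and valid and invalid fits all answer to its wording.

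**Conclusion.** The point holds in this form: for FA and other outcomes measured only at baseline and 6 weeks, the stated model is ill-specified, and its error rate and power depend on an unstated choice of fit and tested term. The consequence ranges from none (the fits equivalent to ANCOVA), through forgone power with correct size (0.80 against 0.92 at rho 0.4), to a type I error of about 6% to 9% in a pooled or random-intercept fit.

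These sizes rest on 21 completers per arm, normal data with equal variances and rho between 0.3 and 0.7. The power figures also rest on reading 0.22 as Cohen's f, with assumed effects of 0, 0.93 and 0.93 SD. The inflation shrinks as rho rises (0.056 at rho 0.9). The structural defect needs none of these assumptions; it follows from the measurement schedule. Because it governs the primary inference, it should be settled before analysis.

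**What to change.** For FA and every outcome measured only at baseline and 6 weeks, state an ANCOVA of the 6-week value on arm and baseline value, plus the electrodiagnostic severity stratum that the Assignment of interventions and blinding section uses in randomisation. Include no time factor, and name the arm comparison as the primary test. A longitudinal model with baseline means constrained equal across arms, and no baseline covariate, is an acceptable alternative.

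Keep a time factor only for the questionnaires, with 6 weeks and 6 months as responses and baseline as the covariate.

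The cost is analysis wording only: no new data and no more patients. With 63 completers the ANCOVA holds about 5% type I error. Under the assumptions above its power is 0.90 to 0.975 for rho from 0.3 to 0.6.

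### Randomisation is stratified by CTS severity but the stated ANCOVA omits it: a design-analysis mismatch that may cost a little power and causes no bias

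*Protocol article*

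**What the plan says.** Under Assignment of interventions and blinding, the article states: "Assignment will be randomised and stratified by electrodiagnostic test severity (mild/moderate) using an online tool". The same section fixes equal allocation: "The allocation ratio will be 1:1:1". It does not say whether blocks are used within the two strata.

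Under Statistical analysis, the two-way repeated measures ANCOVA is described by its terms: "factors time and intervention, adjusted for baseline measurements as a continuous covariate". This model "will be performed to identify differences in primary/secondary outcome measures among groups and over time", so it covers fractional anisotropy and all secondary measures. If normality fails, the article moves to a ranked ANCOVA, again with no mention of severity.

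Under Sample size calculation, the design assumed is "within subjects repeated measures ANOVA with 3 groups & 2 time points", with "d = 0.22, power = 80%, alpha = 0.05". That calculation has no severity term either.

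**The concern.** A trial is normally analysed with the factors by which it was randomised. Stratification aims to make the arms alike on severity, so that severity contributes little to the difference between arms. If severity also predicts the outcome and the model leaves it out, its variance stays in the residual. The standard error is then larger than it need be. Where the arms really are balanced within strata, it also overstates the true sampling variability of the estimate.

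What is at stake is efficiency. With 21 analysable patients per arm planned for 80% power, there is little to spare, since 78 × 0.8 = 62.4 against the 63 required. A few points of power matter at that size, and here they may be had at almost no cost.

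**Working it through.** **Inputs from the article.** Three arms, 1:1:1; two severity strata; model terms time, intervention and baseline value; alpha 0.05; power 80%; 63 evaluable (21 per arm); 78 enrolled.

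**Inputs the article does not give (assumptions).**
- r, the partial correlation of severity with the follow-up value given baseline: shown from 0 to 0.5.
- For the simulation: a 50:50 mild/moderate split, baseline-severity correlation 0.4, baseline-follow-up correlation 0.5, one follow-up value per patient, and effects of 0.84 and 0.42 SD in two arms.

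**Step 1: the plan's own figure.** For the group-by-time interaction, λ = f²·N·m/(1 − ρ), with m = 2 time points and 2 and N − 3 degrees of freedom. If the stated 0.22 is read as Cohen's f and ρ = 0.40, then λ = 0.0484 × 63 × 2/0.60 = 10.16 and power is 80.1%. So 63 can be reproduced, though only with a correlation that the article does not state (0.40 to 0.42 all give 63). Dropout: 63/0.8 = 78.75, against 78 stated. Neither figure involves severity.

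**Step 2: analytic effect of adding severity.** Take 80% power at N = 63 without severity as the anchor. With 2 and 59 degrees of freedom this corresponds to λ = 10.14. Adding severity multiplies λ by 1/(1 − r²) and uses one degree of freedom (2 and 58). The ratio of standard errors, without to with severity, is 1/√(1 − r²). At r = 0.3, λ = 10.14/0.91 = 11.14, power is 83.8% and the ratio is 1.048.

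**Step 3: simulation.** 6,000 trials per setting, 21 per arm, permuted blocks of 3 within strata, testing the overall group effect.

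| r | SE ratio | Analytic power with severity | Type I error without / with | Simulated power without / with |
|---|---|---|---|---|
| 0 | 1.000 | 80.0% | 5.2% / 5.2% | 78.5% / 78.2% |
| 0.1 | 1.005 | 80.4% | 5.3% / 5.5% | 78.0% / 78.5% |
| 0.2 | 1.021 | 81.7% | 4.5% / 5.1% | 78.3% / 79.9% |
| 0.3 | 1.048 | 83.8% | 3.9% / 5.0% | 77.6% / 81.1% |
| 0.5 | 1.155 | 90.4% | 2.4% / 4.8% | 78.6% / 88.9% |

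At r = 0.3 the mean model standard error without severity is 0.268, against an empirical SD of 0.258 to 0.265, so it is about 1% to 4% too large. With severity the model standard error is 0.256.

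**Step 4: dependence on balance.** With allocation not balanced by stratum and r = 0.3, the model without severity has a simulated type I error of 5.0%. The conservatism disappears, but precision is still lost: the empirical SD is 0.268 without severity and 0.258 with it.

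**Step 5: a second simulation.** 8,000 trials per setting, exercise against advice only, exactly 11 mild and 10 moderate per arm, assumed difference 0.88 SD. With severity explaining 5% or 10% of the variance left after baseline (r = √0.05 = 0.22 or √0.10 = 0.32), the type I error without severity was 4.4% or 4.0%. Power rose from 80% to 82%, or from 81% to 84%, when severity was added. This agrees with Step 3.

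**The case against.** The strongest reply is that the harm is conditional and probably small. The model already adjusts each outcome for its own baseline, which may absorb much of what severity would explain. At r of 0.1 or less the loss is practically nil. A loss of about 10 points needs r near 0.5, and nothing in the article supports that for fractional anisotropy. This stands, and it sets the size of the point.

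A second reply is that this is a condensed article and that an analysis plan, not shown, may add severity. That is possible. But the article does more than stay silent: it names the factors and the covariate, and that specification does not match the randomisation it describes.

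Several stronger readings are tempting and do not hold:

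- *Standard errors are too large and power is lost, whatever the data.* This requires severity to be prognostic beyond baseline, and overstated standard errors also require balance within strata. The article establishes neither, and dropout would disturb such balance.
- *The benefit of stratifying is wasted.* In the exact-balance simulation, power without the severity term was 80% and 81% at 5% and 10% of variance explained, so the unadjusted analysis keeps part of the benefit.
- *Nerve-conduction outcomes suffer more because the strata are cut from conduction measures.* This is not shown. Those outcomes are adjusted for their own baselines. In a linear model, a cut of the same baseline measure adds nothing, while a cut of a different measure may add something. Motor terminal latency, which separates mild from moderate, is not among the outcomes listed under Neurophysiological function.
- *Severity is missing from the multiple imputation.* The article lists no imputation variables, so nothing can be concluded.

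**Conclusion.** The mismatch is real: allocation is stratified by severity, and the stated ANCOVA and its ranked fallback do not include it. For an assumed r of 0 to 0.3, the cost is about 0 to 4 percentage points of power at 63 evaluable patients. If the arms are balanced within strata, the type I error is about 4% to 5% instead of 5%. These sizes rest on the assumed r, on one follow-up value per patient, and on the simulation settings listed above.

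A reader might infer that the planned analysis is biased or invalid, or that the trial is undersized because of this. The article does not support that. The omission biases no treatment comparison, does not inflate the type I error, and does not enter the calculation of 63. The point is an improvement worth making, of small to moderate and uncertain gain.

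**What to change.** Add electrodiagnostic severity (mild/moderate, as recorded for randomisation) as a fixed factor in the ANCOVA for the primary outcome and for the secondary outcomes, and carry it into the ranked ANCOVA fallback. Record the change before any unblinded analysis so that it cannot appear data-driven. If the investigators prefer to leave severity out, they should say why.

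The cost is one degree of freedom and no new data collection. If severity turns out not to be prognostic, the penalty is negligible: 78.5% against 78.2% simulated power at r = 0, a difference of the order of simulation noise. Analytically, the lost degree of freedom lowers power by less than 0.1 point.
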